## 4.2 Study Duration

The total duration of the study per study patient is up to 47 days from Screening/Randomization (up to 12 days [Day -12] for an asymptomatic patient) through to the end of the Follow-up Period (Day 35); see [Figure 4](#).

## 4.3 Study Procedures

Details of the individual study procedures are provided in [Section 4.3.1](#) through [Section 4.3.11](#). Timing for when each procedure is to be conducted is presented in the SOA below ([Table 1](#)). All self-assessments and patient-reported responses will be recorded in TrialPace™ using the patient's unique log-in and password.

**Table 1. Schedule of Assessments**

| Assessment                                                                       | Part 1               | Part 2                                      |       |               |               |                |                |                  |                |                |                | ET Visit       |
|----------------------------------------------------------------------------------|----------------------|---------------------------------------------|-------|---------------|---------------|----------------|----------------|------------------|----------------|----------------|----------------|----------------|
|                                                                                  | Screening            | Intake Period:
(SSC + KB109 or SSC Only) |       |               |               |                |                | Follow-up Period |                |                |                |                |
|                                                                                  | Up to
D -12 to -1 | D 1
(+1 D)                               | D 2   | D 3
(±1 D) | D 7
(±1 D) | D 10
(±1 D) | D 14
(±3 D) | D 15 to
D 20  | D 21
(±1 D) | D 28
(±1 D) | D 35
(±1 D) |                |
| Informed Consent                                                                 | X                    |                                             |       |               |               |                |                |                  |                |                |                |                |
| Registration in TrialPace™                                                       | X                    |                                             |       |               |               |                |                |                  |                |                |                |                |
| Demographics and medical history                                                 | X                    |                                             |       |               |               |                |                |                  |                |                |                |                |
| Confirm eligibility criteria                                         | X                    |                                             |       |               |               |                |                |                  |                |                |                |                |
| Randomization                                                        | X                    |                                             |       |               |               |                |                |                  |                |                |                |                |
| Consume KB109 for patients in this group (SSC + KB109)                           |                      | X                                           | Daily |               |               |                | X              |                  |                |                |                |                |
| Physical Examination                                                             | X        | X                               |       |               |               |                | X  |                  |                |                | X  | X  |
| Height, weight, BMI calculation                                                  | X                    |                                             |       |               |               |                |                |                  |                |                |                |                |
| Patient-assessed COVID-19 Signs (temperature and oxygen saturation)  | X                    | X                               | Daily |               |               |                | X              |                  | X              | X              | X              | X              |
| Patient-assessed Wellness Check COVID-19 Condition                   | X                    | X                               | Daily |               |               |                |                |                  |                |                |                | X              |
| Patient Global Impression on COVID-19 Condition                      |                      |                                             | Daily |               |               |                |                |                  |                |                |                | X              |
| Quality of life indices                                                          |                      |                                             |       |               |               |                | X              |                  |                |                | X              |                |
| Healthcare utilization questions                                                 |                      |                                             | Daily |               |               |                |                |                  |                |                |                | X              |
| Patient-assessed Bedrest Time                                                    |                      | X                               | Daily |               |               |                |                |                  |                |                |                | X              |
| Nasal swab                                                           | X                    |                                             |       |               |               |                | X              |                  |                |                | X              |                |
| Oropharyngeal swab                                                   | X                    |                                             |       |               |               |                | X              |                  |                |                | X              |                |
| Blood samples                                                        | X                    |                                             |       |               |               |                | X              |                  |                |                | X              |                |
| Urine Pregnancy test                                                | X                    |                                             |       |               |               |                |                |                  |                |                |                |                |
| Telemedicine Visit                                                  |                      | X                                           |       |               |               |                | X              |                  |                |                | X              | X              |

|                             |                      |                 |  |   |   |   |                 |                 |   |   |                 |  |
|-----------------------------|----------------------|-----------------|--|---|---|---|-----------------|-----------------|---|---|-----------------|--|
| Wellness Visit by telephone |                      | X  |  | X | X | X | X  |                 | X | X | X  |  |
| AE review                   | Throughout the study |                 |  |   |   |   |                 |                 |   |   |                 |  |
| Concomitant medication      | Throughout the study |                 |  |   |   |   |                 |                 |   |   |                 |  |
| Return of study product     |                      |                 |  |   |   |   |                 | X  |   |   |                 |  |

Abbreviations: AE = Adverse event; BMI = Body mass index; D = Day; ET = Early termination; KaSK = Kaleido at-home Study Kit; SSC = Supportive self-care

Note that the patient will have had a SARS-CoV-2 test (RT-PCR test, antigen test or equivalent test to detect active infection). Positive SARS-CoV-2 test results from a local testing clinic that is not the study site location may be used to determine eligibility virtually (not at site). Hospital, academic, or industry-based assays will be acceptable for the diagnosis of COVID-19; home-based tests are not accepted for this study.

 If symptomatic and currently positive for COVID-19 diagnostic test, the patient must not report significant improvement in their cardinal COVID-19 symptoms in the 48 hours immediately prior to randomization.

The physical examination at screening can be a) a basic face-to-face physical examination at the patient's outpatient clinic visit, b) based on findings from a physical examination conducted as part of the standard patient intake evaluation into an emergency department or testing clinic (at the discretion of the Investigator), or c) an abbreviated telemedicine-based physical examination (see [Section 4.3.3](#) for further details).

Abbreviated telemedicine-based physical examinations (see [Section 4.3.3](#)).

 patients will receive the thermometer and pulse oximeter device in the KaSK delivered to their home prior to Day 1, at which time they will begin to record their temperature and oxygen saturation in the TrialPace™ diary.

These measures should be completed prior to the first dose of KB109 for patients in the SSC + KB109 group.

The Patient-assessed Wellness Check COVID-19 Condition ([Section 4.3.4](#)) includes patient-assessed COVID-19 symptoms and signs. Responses are recorded in TrialPace™.

The Patient Global Impression on COVID-19 Condition (PGIC) responses are recorded in TrialPace™.

See [Section 4.3.9](#) for the blood tests. If feasible blood samples for clinical chemistries, biomarkers and serological measures of immunity, and nasal/oropharyngeal swabs for quantitative viral load assessments (research purposes only) will be collected; sample collection may occur at the patient's home by a healthcare professional, remotely, or at the study site or clinic.

Pregnancy status for all females of childbearing potential (as defined in accordance hospital policies and procedures at the patient's outpatient clinic visit) may be collected by patient self-report or urine pregnancy test.

Telemedicine Visits will take place on Days 1, 14, 35, and at an Early Termination Visit, and may also take place throughout the study as needed.

Wellness visit by telephone will be included in the telemedicine visit when they fall on the same day.

Patients will return the SP during the follow-up period.

### **4.3.1 Patient Demographics and Baseline Characteristics**

Demographic information and baseline characteristics obtained will include age, sex, race, ethnicity, weight, and height.

### **4.3.2 Medical History and Concomitant Medications/Procedures**

The medical history of the patient will be obtained by the PI or qualified designee. Medical history will be recorded and should include prior/existing medical conditions and surgical procedures, physical examination findings and clinically significant laboratory abnormalities.

Medication history information to be obtained also includes any medication (prescription or nonprescription) and any dietary or nutritional supplement relevant to eligibility criteria stopped at or within 28 days before signing of informed consent.

Concomitant medications and procedures will be recorded throughout the study.

### **4.3.3 Physical Examination**

At screening, in order to minimize contact between patients and providers, physical examinations to determine eligibility may be conducted via one of the following methods:

- a) A basic face-to-face physical examination performed by a qualified healthcare provider in accordance hospital policies and procedures at the patient's outpatient clinic visit. The examination will include a general assessment (e.g., overall appearance, orientation), pulmonary auscultation, and an assessment for work of breathing (e.g., speech cadence, lifting hands above head, observing ambulation).
- b) At the discretion of the Investigator, findings from a physical examination conducted as part of the standard patient intake evaluation at an emergency department or testing clinic can be used to assess relevant inclusion/exclusion criteria provided the physical examination was done within 24 hours of consent and diagnostic COVID-19 testing.
- c) An abbreviated telemedicine-based physical examination comprising a general assessment (e.g., overall appearance, orientation) and an assessment for work of breathing (e.g., speech cadence, lifting hands above head), and will be performed according to guidelines outlined via the central telemedicine provider.

Abbreviated telemedicine-based physical examinations will be conducted for all post-screening assessments (see [Table 1](#)). All findings from this examination will be recorded on source documents.

Any new abnormal findings upon physical examination noted after informed consent is obtained and deemed clinically meaningful by the PI or designee may be recorded in the eCRF as an AE.

#### **4.3.4 Patient-assessed COVID-19 Condition**

Patients will begin reporting COVID-19-related symptoms in TrialPace™ after consent to the study (Part 1) following the outpatient clinic visit for evaluation of suspected COVID-19 infection. Responses should be recorded consistently upon waking in the morning. Patients should always complete the Patient-assessed COVID-19 score prior to the PGIC.

Following randomization in Part 2 of the study, patient-reported COVID-19 symptom measurements will continue to be performed in the morning upon waking and according to the SOA ([Table 1](#)). See [Section 6.7](#) regarding patient instructions in the event COVID-19 symptoms worsen.

##### **4.3.4.1 Patient-assessed COVID-19 Symptom Score**

Symptom severity will be assessed based on how the patient is feeling at the moment. This will be recorded in TrialPace™.

Patients will self-assess the following 8 cardinal symptoms known to be associated with COVID-19 ([CDC 2020](#)):

1. Fever
2. Chills/Repeated shaking with chills
3. Cough
4. Shortness of breath
5. Headache
6. Muscle pain
7. Anosmia/ageusia
8. Sore throat

Additionally, patients will also report on the following 5 symptoms:

1. Gastrointestinal disturbance/symptoms (other than diarrhea as this will be assessed separately)
2. Diarrhea
3. Fatigue
4. Nasal congestion
5. Chest tightness

Patients will be instructed to rate their symptoms on a scale of 0-3 where:

- 0: Absent (no symptoms evident)
- 1: Mild (symptom present but easily tolerated)
- 2: Moderately severe (definite awareness of symptoms; bothersome but tolerable)
- 3: Very severe (hard to tolerate; interferes considerably with daily activity)

#### 4.3.4.2 Patient-assessed COVID-19 Signs

Following randomization, selected patient-assessed COVID-19 signs will be performed daily, upon waking, as needed and according to the SOA ([Table 1](#)).

Patients will self-assess temperature and oxygen saturation according to the instructions for use of the thermometer and pulse oximeter included in their KaSK and will record measures in TrialPace™. See [Section 6.7](#) regarding patient instructions in the event COVID-19 signs and symptoms worsen.

#### 4.3.5 Patient Global Impression on COVID-19 Condition (PGIC)

From Day 2 onwards, daily COVID-19 symptom severity will be assessed reflectively based on how the patient felt over the past 24 hours. This will be recorded in TrialPace™.

Over the past 24 hours, the patient would be asked to rate overall COVID-19 condition change into 7 categories: Very much worse, Much worse, minimally worse, no change, minimally improved, much improved, Very much improved.

#### 4.3.6 Quality of Life Indices

Following randomization, on Days 14 and Day 35, during the telemedicine visit, the telemedicine provider will ask the following questions to assess QOL ([Table 1](#)). Telemedicine providers must read the questions as they are written and cannot provide the patient with assistance on interpreting the meaning of questions as it is paramount that the interpretation be left up to the patient.

- 1.) Overall, how would you rate your health during the past 14 (or 21) Days?  
*Rated as: Excellent, Very Good, Good, Fair, Poor, Very Poor*
- 2.) During the past 14 (or 21) Days, how much did your COVID-19 symptoms limit your physical activities (such as walking or climbing stairs)?  
*Rated as: Not at all, Very little, Somewhat, Quite a lot, Could not do physical activities*
- 3.) How much bodily pain have you had during the past 14 (or 21) Days?

*Rated as: None Very mild, Mild, Moderate, Severe, Very severe*

- 4.) During the past 14 (or 21) Days, how much energy did you have?

*Rated as: Very much, Quite a lot, Some, A little, None*

- 5.) During the past 14 (or 21) Days, how much have you been bothered by emotional problems (such as feeling anxious, depressed or irritable)?

*Rated as: Not at all, Slightly, Moderately, Quite a lot, Extremely*

- 6.) Thinking about any emotional problems you may have had such as feeling, anxious, depressed or irritable, for how many days during the past 14 (or 21) Days was your emotional health not good?

*Rated as number of days from 1-14 days at the end of the Intake Period (Day 14) and 15-35 days at the end of the Follow-up Period.*

- 7.) Thinking about your overall physical health for how many days during the past 14 (or 21) Days was your physical health not good?

*Rated as number of days from 1-14 days at the end of Intake Period (Day 14) and 15-35 days at the end of the Follow-up Period.*

- 8.) During the past 14 (or 21) Days, how much did your COVID-19 symptoms interfere with your normal sleep patterns?

*Rated as: Not at all, Slightly, Moderately, Quite a lot, Extremely*

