## 4 STUDY DESIGN

### 4.1 Overall Design

This study is a randomized, controlled, multi-site, open label clinical study. It is intended to assess KB109 on safety as well as measures of signs, symptoms, healthcare utilization (including hospitalizations), laboratory/biochemical indices and QOL measures in outpatients who have tested positive with COVID-19, have mild-to-moderate disease, and have been advised to manage their disease at home with SSC under quarantine protocols set forth by the CDC ([CDC 2020](#)) or local ordinances or practices as advised by their healthcare provider.

Approximately 350–400 patients will be randomized (1:1) to receive either SSC + KB109 or remain on SSC alone. The randomization will be stratified by site/center, age subgroup ( $\geq 18$  to  $<45$  years,  $\geq 45$  to  $<65$  years,  $\geq 65$  years), and comorbidity status (Yes, No); see [Section 8.1](#) for

further details. The study consists of a Screening/Randomization Visit, Intake Period (14 Days) followed by a 21-day Follow-up Period (Figure 4).

Details of the procedures and assessments conducted during the study are provided in Section 4.3, and the timing for each is presented in the Schedule of Assessments (SOA; Table 1) and summarized in Figure 4.

To be eligible for the study, patients must be at least 18 years of age, have tested positive for COVID-19, and be medically stable at study entry per eligibility criteria. Patients must have also been advised by a healthcare provider that self-management of COVID-19 is indicated; eligibility criteria are detailed in Section 5.1 and Section 5.2.

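### QOL items 6 and 7 (Section 4.3.6): the stated answer ranges, 1 to 14 and then 15 to 35, do not fit day counts over 14 and 21 days

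*Protocol*

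**What the plan says.** Section 4.3.6 of the protocol sets out eight QOL questions and when they are put: "on Days 14 and Day 35, during the telemedicine visit, the telemedicine provider will ask the following questions to assess QOL". Two of the eight ask for a number of days.

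- Item 6 asks "for how many days during the past 14 (or 21) Days was your emotional health not good". The line below it puts the answer between 1 and 14 at Day 14, and gives the range for the second visit as "15-35 days at the end of the Follow-up Period".
- Item 7 asks "for how many days during the past 14 (or 21) Days was your physical health not good". Its answer line sets the same two ranges: "Rated as number of days from 1-14 days at the end of Intake Period (Day 14) and 15-35 days at the end of the Follow-up".

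Section 4.1 fixes the lengths of the two periods: "Intake Period (14 Days) followed by a 21-day Follow-up Period". It also labels the Follow-up Period as study Days 15 to 35.

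On how the questions are put, Section 4.3.6 says: "Telemedicine providers must read the questions as they are written and cannot provide the patient with assistance on interpreting the meaning of questions".

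Section 3.2.3 lists the individual QOL measures among the exploratory endpoints, and Section 8.4 leaves exploratory methods to a separate document. No other section gives a different range for these two items or mentions a zero answer.

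**The concern.** A number of days within a recall window of w days can be any whole number from 0 to w. Neither stated range has that form. The Day 14 range starts at 1. The Day 35 range starts above most of the answers a patient could give and ends well beyond the length of the window.

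The neighbouring items make the gap plain. Items 2, 3, 5 and 8 each offer a lowest category meaning no limitation, no pain, no bother or no interference. A patient who reports no emotional trouble at all on item 5 has no consistent answer to item 6 if the stated range is followed.

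What is at stake is the accuracy of two items at both visits at which they are asked. QOL has no baseline assessment in Table 1, so Days 14 and 35 are all the data there are. This is also a matter the protocol itself fixes: an answer scale acts when the data are captured, and a later analysis plan cannot restore a count that the form refused. Section 9.2.5 says the data system carries automatic range checks. If those were programmed from Section 4.3.6, true low counts would be rejected.

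**Working it through.** No power, sample-size or error-rate formula is involved. The check compares sets of whole numbers.

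**Inputs**
- Recall windows: 14 days at Day 14 and 21 days at Day 35 (stems of items 6 and 7).
- Stated answer ranges: 1 to 14 and 15 to 35 (answer lines of items 6 and 7).
- Length of the Follow-up Period: 21 days (Section 4.1). The labels agree: 35 − 15 + 1 = 21.

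**Trying to reproduce the stated 15 to 35.** As a count over 21 days the range should be 0 to 21, so the figure does not reproduce. As calendar labels it does: the first day after Intake is 14 + 1 = 15, and the last day of Follow-up is 14 + 21 = 35. The range therefore matches study-day labels, not a count.

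**Comparison at each visit**

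| | Day 14 | Day 35 |
|---|---|---|
| Possible counts | 0 to 14 (15 values) | 0 to 21 (22 values) |
| Stated range | 1 to 14 (14 values) | 15 to 35 (21 values) |
| Overlap | 1 to 14 (14 values) | 15 to 21 (7 values) |
| Possible but not on the scale | 0 (1 value) | 0 to 14 (15 values) |
| On the scale but not possible | none | 22 to 35 (14 values) |

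At Day 35, 15/22 = 68% of the possible counts cannot be recorded, and 14/21 = 67% of the stated values exceed the window. These are shares of scale values, not of patients. The documents give no distribution of the answers.

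**Size of the distortion if the ranges were enforced.** At Day 14, a true 0 moved to the lowest permitted value becomes 1, a shift of 1 day. At Day 35, a true count c below 15 moved to the lowest permitted value shifts by 15 − c days: 15 days for c = 0 and 1 day for c = 14. The lowest recordable answer would be 15/21 = 71% of the window.

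**Alternative reading tried.** Suppose the Day 35 answer were cumulative over Days 1 to 35. Possible counts are then 0 to 35, and 22 to 35 become possible, but 0 to 14 still cannot be recorded. This reading also contradicts the stem, which asks about 21 days.

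**The case against.** The best case on the other side is that the answer lines only name the counting window. The figures 1 to 14 and 15 to 35 are exactly the study-day labels of the two periods, so the lines could mean the number of days out of study Days 1 to 14, and then out of Days 15 to 35. That agrees with the stems, allows zero, and leaves nothing biased. It is very likely how the wording arose. But it is not what the text says. Both lines give a number of days from one figure to another, which is an answer range, and staff may not help the patient interpret the question.

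A second objection carries more weight. The stem is read aloud, and a patient may simply answer none, or three. The protocol does not say that the answer line is a forced choice or that the eCRF rejects values outside it, and the form is not among the documents. This stands. Any bias depends on how the form was built.

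Third, a reader might infer that both ranges are impossible. That fits 15 to 35 only. Every value from 1 to 14 is a possible count over 14 days, and the fault there is the missing zero.

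Fourth, a reader might infer that Follow-up is bound to look worse than Intake, because the Day 35 minimum of 15 lies above the Day 14 maximum of 14, or that group differences are certainly compressed. The documents do not support either as fact. Both would need the ranges to be enforced, and the protocol plans no comparison of QOL between Intake and Follow-up.

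**Conclusion.** The answer ranges of items 6 and 7 are wrong as written and should be corrected. The contradiction between stem and range can be seen within Section 4.3.6 and rests on no assumption. At Day 14 one possible answer, zero, is missing. At Day 35 the range leaves out 0 to 14 and admits 22 to 35.

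The effect on the data is conditional. If the capture form applies the stated ranges, patients with no bad days at Day 14, or with 0 to 14 bad days at Day 35, cannot be recorded correctly, and both items would be biased upwards. If the form accepts any count within the recall window, the data are sound and only the text needs correcting. The protocol does not show which applies, so it would go too far to say that patients were forced to report at least 15 bad days.

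Priority is low. Two of eight QOL questions in an exploratory endpoint are affected. The primary endpoint, the secondary endpoints and the sample size are not.

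**What to change.** In Section 4.3.6, items 6 and 7, give the range as 0 to 14 days at the Day 14 visit and 0 to 21 days at the Day 35 visit. Set the same limits as range checks in the eCRF.

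Then establish how the form was built. If it accepted any count within the window, only values above 21 at Day 35 need a query. If it enforced the stated ranges, querying values outside the new limits is not enough: an answer pushed up to 1 at Day 14, or to 15 to 21 at Day 35, lies inside the new limits and would pass. In that case, review the entries of 1 at Day 14 and of 15 to 21 at Day 35 together with those above 21, or flag the two items as unreliable for the visits concerned.

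The cost is one answer line in each of two items and a range check, with no new assessments. The review of entered values is extra work only if the form did enforce the ranges.
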